### 2.2 Secondary objectives

The secondary objectives of the study are....

....to observe and compare clinical efficacy by means of postoperative infection rates, use of postoperative antibiotics, length of hospital stay and health status for patients transfused with Sangvia® blood, no blood and/or allogeneic blood.

....to observe and compare clinical efficacy by means of systemic postoperative haemoglobin levels for patients transfused with Sangvia® blood, no blood or allogeneic blood.

....to collect details in health care utilisation (medications, in-patient service use, blood management) that would allow a calculation and comparison of cost-consequences applying either alternative in the blood management and from the perspective of the payer

....to observe and compare safety by means of adverse events, highlighting renal failures and events potentially related to transfusion, body temperature and other clinical complications for patients transfused with Sangvia® blood, no blood or allogeneic blood.

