#### 6.1.2 Covariates and prognostic variables

Bleeding volume or complexity of surgery, i.e. surgery time, are considered to possibly influence outcome of the primary variable why stratification for either primary or secondary/revision hip surgery will be made at each recruiting clinic to ensure equal distribution in the two groups. Subgroup analyses of type (primary and secondary) and complexity (easy < 1 hour, medium 1-2 hours and complex > 2 hours) of surgery are planned to further investigate the correlation between the primary outcome and these factors.

Age is also an potential factor that may have an impact on the outcome of the primary variable. It is however considered that randomization as such will ensure approximately equal age distribution in the two treatment groups. Differences in age between the treatment groups will be evaluated and tested using Wilcoxon rank sum test in the analysis.

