## 6.3 Description of analysis sets

The study will be analyzed using a Per Protocol (PP) and an All Patient Treated (APT) approach. Subjects fulfilling the inclusion criteria but none of the exclusion criteria and have been treated according to the protocol without any major deviations (e.g. wrongful transfusion decision of bank blood) will be included in the PP analysis set. All patients will be included in the APT analysis set. Treatment efficacy related conclusions will be based on the results from the PP analysis and demography and treatment safety related conclusions will be based on the results from the APT analysis.

Subgroup analyses of type (primary and secondary) and complexity (easy < 1 hour, medium 1-2 hours and complex > 2 hours) of surgery will be performed as well as analyses per clinic and per blood transfusion type (none, autologous, allogeneic and combinations).

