## 6.5 Determination of sample size

The primary variable and objective is the base for the sample size calculation. The sample size formula used is referred to in Lachin 1981.

$$N = \frac{(Z_{\alpha} + Z_{\beta})^2 4\bar{\pi}(1 - \bar{\pi})}{(\pi_s - \pi_c)^2}$$

Where:

N = total number of patients

$Z_{\alpha} = 1.96$  ( $\alpha = 0.05$ )

$Z_{\beta} = 1.2816$  ( $1 - \beta = 0.90$ )

$$\bar{\pi} = \frac{\pi_s + \pi_c}{2}$$

An estimation normal use of allogeneic blood of 21% is based on reported values in the literature. It is acknowledged that in revision surgery a higher percentage of allogeneic blood transfusions is seen than in primary total hip replacements. Because revision patients requiring serious bone grafting are excluded, the percentage of revision patients is expected to be just slightly higher than for the average primary total hip. A high number of revision, e.g. a maximum of 30%, in the total group of patients is considered to have limited effect of the total transfusion rate but are accounted for in the 21% assumed for the total group. The expected values of transfusion rate in the Sangvia® group is estimated to lie around 7%. Accordingly, imputing the values for the estimated transfusion rates in the test and control group generates a mean transfusion rate value of 14%. The sample size necessary for detection of this expected difference in transfusion rate frequency is calculated to 260 patients (5% significance level, two-sided hypothesis, 90% power). Additional 40 patients will be included in the study to compensate for drop-out. In summary, 300 patients will be included in total and 150 in each treatment group.

The transfusion rate of bank blood is considered to vary dependent on type and complexity of surgery. Greatest normal use and differences between the groups are expected in the subgroup with medium (surgery duration 1-2 hours) to complex (surgery duration more than 2 hours) surgery complexity why power are considered to be adequate for the planned subgroup analyses in these groups.

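### Secondary objectives and one planned analysis group patients by blood actually received, which contradicts the randomised comparisons elsewhere and is confounded by blood loss; the power claimed for the surgery-duration subgroups has no figures behind it

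*Protocol*

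**What the plan says.** **Grouping by blood received.** Protocol section 2.2 (repeated in the synopsis) sets the first secondary objective as a comparison of infection, antibiotic use, length of stay and "health status for patients transfused with Sangvia® blood, no blood and/or allogeneic blood". The haemoglobin and safety objectives use nearly the same grouping. Section 6.3 then adds subgroup analyses by type and complexity of surgery "as well as analyses per clinic and per blood transfusion type (none, autologous, allogeneic and combinations").

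**Grouping by randomised arm.** The operative sections read differently. Section 4.3 derives antibiotic use per arm and compares length of stay and haemoglobin between treatment groups. Section 4.5 compares EQ-5D between the two treatment groups. Section 6.2 tests the secondary objectives with hypotheses like the primary one, which sets Sangvia against control. Section 6.4 tests continuous variables between the parallel groups.

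**Duration subgroups.** Section 6.1.2 states that subgroup analyses of surgery type and "complexity (easy < 1 hour, medium 1-2 hours and complex > 2 hours) of surgery are planned". Section 6.5 expects the greatest use of bank blood, and the greatest differences, in medium to complex surgery, "why power are considered to be adequate for the planned subgroup analyses in these groups". It gives no subgroup size, transfusion rate or power figure.

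**The concern.** Which blood a patient receives is settled after randomisation. Under sections 3.1 and 3.4.2 allogeneic blood is given on a haemoglobin trigger or on symptoms, and section 3.2 justifies the primary variable by saying that it reflects blood loss. Test-arm blood is returned routinely. The transfusion-type classes therefore sort patients by how much they bled as well as by arm. If conclusions on infection, length of stay or safety were drawn from them, a device with no effect could look protective against allogeneic blood.

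Surgery time has a milder form of the same problem. Patients are allocated once eligibility is established (section 3.5), stop time is recorded afterwards (section 3.1), and the site team knows the arm (section 3.6.1).

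The power sentence matters because it invites a confirmatory reading of subgroup p-values that the protocol has not shown it can support.

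**Working it through.** **1. The plan's own figure.** Inputs from section 6.5: "5% significance level, two-sided hypothesis, 90% power" (Z values 1.96 and 1.2816), control rate 21%, test rate 7%, mean 14%.

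N = (1.96 + 1.2816)² × 4 × 0.14 × 0.86 / 0.14² = 258.2

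The stated 260 is reproduced. With "300 patients will be included in total and 150 in each treatment group", exact two-sided Fisher power for the whole trial is 93.1%. The subgroup sentence contains no figure, so there is nothing to reproduce for it.

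**2. Who falls in each transfusion-type class.** At 150 per arm, the planned rates, and routine return of blood in the test arm:

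| Class | Arm | Expected number |
|---|---|---|
| None | control | 150 × 0.79 = 118.5 |
| Allogeneic only | control | 150 × 0.21 = 31.5 |
| Autologous only | test | 150 × 0.93 = 139.5 |
| Autologous plus allogeneic | test | 150 × 0.07 = 10.5 |

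'None' and 'allogeneic only' are in effect the control arm split by the primary outcome. 'Autologous only' is the test arm without those who needed bank blood. (Test patients whose blood was not returned on medical judgement would be the few exceptions.) For the primary outcome the split is circular: the transfusion rate is 0% or 100% in each class by definition.

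**3. Size of the confounding, illustrated.** Assumptions, not protocol figures: 21% of patients in each arm are bleeders with 8% infection risk; the other 79% have 2%; the device has no effect on infection; all control bleeders receive allogeneic blood; in the test arm 7% of patients, all bleeders, still need it, leaving 14% who bleed but avoid it.

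- Either arm: 0.21 × 8% + 0.79 × 2% = 3.26%
- Autologous only: (0.14 × 8% + 0.79 × 2%) / 0.93 = 2.9%
- Allogeneic only: 8%
- Apparent risk ratio: 2.9 / 8 = 0.36, where the true ratio between arms is 1
- Control patients with no blood: 2%, so against this class the same inert device would look harmful (2.9 / 2 = 1.45)

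A second assumed model, in which blood loss drives both transfusion and infection on a continuous scale, agrees in direction: 4.9% autologous only against 8.6% allogeneic only, with both arms at 5.3%.

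**4. Power in the duration subgroups.** Inputs from section 6.5: "An estimation normal use of allogeneic blood of 21% is based on reported values in the literature", and 7% in the Sangvia group. Subgroup shares and rates are assumed, because none are given; they are constrained to average 21% and 7% over 300 patients. Power is exact two-sided Fisher.

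| Assumed scenario | Group | Per arm | Rates | Power |
|---|---|---|---|---|
| Equal thirds, threefold ratio, no transfusion in easy surgery (21% × 1.5, 7% × 1.5) | medium or complex alone | 50 | 31.5% v 10.5% | 67% |
| Same | medium and complex pooled | 100 | 31.5% v 10.5% | 95% |
| Half the patients easy at 7% v 7%, a quarter each medium and complex (totals 0.5 × 7 + 0.5 × 35 = 21% and 7%) | medium or complex alone | 37 to 38 | 35% v 7% | 82% to 83% |

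A wider set kept the threefold ratio, let rates rise with duration (easy:medium:complex from 1:1.5:2 to 1:3:6) and used four assumed splits. Medium alone had 33% to 73%, complex alone 33% to 79%, and the pooled group 86% to 92%.

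**The case against.** The strongest reply is that the sections which govern the analysis already compare randomised arms: antibiotics, length of stay, haemoglobin and EQ-5D in sections 4.3 and 4.5, and the tests in sections 6.2 and 6.4. This stands. A reader of section 2.2 alone might infer that the whole secondary analysis is non-randomised; the document does not support that. What remains is a contradiction between the objectives and the tests, plus one extra analysis in section 6.3 that names no outcome or test and is not called descriptive.

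A reader might also infer that the duration subgroups compare bleeders with non-bleeders. They do not. Within a duration band the comparison is still test against control, and it is biased only if allocation changes surgery time, which nothing in the protocol says. Surgery type and clinic are baseline stratification factors and are untouched.

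Finally, one might conclude that adequate subgroup power is impossible at 21% and 7%. The third scenario in the table disproves this, because section 6.5 expects larger differences in these strata and a constant threefold ratio need not hold. Its wording can also be read as one pooled medium-to-complex group. Against that, sections 6.1.2 and 6.3 list medium and complex as separate levels, and the sentence offers no basis on which to choose among these scenarios.

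**Conclusion.** The point holds in three limited parts.

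- **Blood received.** The objectives contradict sections 4.3, 4.5, 6.2 and 6.4, and the transfusion-type analysis in section 6.3 is confounded by blood loss and circular for the primary outcome. That follows from the protocol's own rules. The risk ratio of 0.36 shows the mechanism under invented infection risks and is not a forecast.
- **Surgery time.** It is a post-allocation variable in an unblinded theatre. This is a potential bias, conditional on allocation affecting duration.
- **Power.** The statement is unsupported. For each level taken alone it fails under proportional rates (67% in the simple case, 33% to 79% across the graded ones). It could hold for a pooled group or with a larger relative effect in those strata.

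The primary comparison and the sample size are not affected, so this should be corrected but does not threaten the main result.

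**What to change.** 1. Reword the secondary objectives in section 2.2 and the synopsis as comparisons of the randomised arms, consistent with sections 6.2 and 6.4.
2. In section 6.3, label analyses by transfusion type as descriptive, with no efficacy or safety conclusions drawn from them.
3. Label the duration subgroups exploratory, and rely on the pre-randomisation primary/secondary stratum for questions of effect modification.
4. In section 6.5, delete the sentence on subgroup power, or replace it with the assumed subgroup sizes and rates and the computed power, saying whether medium and complex are pooled.

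The cost is wording only: no change to design, data collection or sample size. The sponsor gives up claims against allogeneic blood drawn from the transfusion-type tables.

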## 6.4 Method of statistical analysis

Fischer Exact test will be used to test frequencies of dichotomous response variables. The non-parametric Wilcoxon Rank Sum test will be used to test differences in continuous response

variables between the parallel treatment groups. Wilcoxon Signed Rank test will be used to test differences over time within each treatment group. P-values equal to or below 0.05 are considered as statistically significant.

## 6.5 Determination of sample size

The primary variable and objective is the base for the sample size calculation. The sample size formula used is referred to in Lachin 1981.

$$N = \frac{(Z_{\alpha} + Z_{\beta})^2 4\bar{\pi}(1 - \bar{\pi})}{(\pi_s - \pi_c)^2}$$

Where:

N = total number of patients

$Z_{\alpha} = 1.96$  ( $\alpha = 0.05$ )

$Z_{\beta} = 1.2816$  ( $1 - \beta = 0.90$ )

$$\bar{\pi} = \frac{\pi_s + \pi_c}{2}$$

An estimation normal use of allogeneic blood of 21% is based on reported values in the literature. It is acknowledged that in revision surgery a higher percentage of allogeneic blood transfusions is seen than in primary total hip replacements. Because revision patients requiring serious bone grafting are excluded, the percentage of revision patients is expected to be just slightly higher than for the average primary total hip. A high number of revision, e.g. a maximum of 30%, in the total group of patients is considered to have limited effect of the total transfusion rate but are accounted for in the 21% assumed for the total group. The expected values of transfusion rate in the Sangvia® group is estimated to lie around 7%. Accordingly, imputing the values for the estimated transfusion rates in the test and control group generates a mean transfusion rate value of 14%. The sample size necessary for detection of this expected difference in transfusion rate frequency is calculated to 260 patients (5% significance level, two-sided hypothesis, 90% power). Additional 40 patients will be included in the study to compensate for drop-out. In summary, 300 patients will be included in total and 150 in each treatment group.

The transfusion rate of bank blood is considered to vary dependent on type and complexity of surgery. Greatest normal use and differences between the groups are expected in the subgroup with medium (surgery duration 1-2 hours) to complex (surgery duration more than 2 hours) surgery complexity why power are considered to be adequate for the planned subgroup analyses in these groups.

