## 6.2 Description of outcome variables in relation to objectives and hypotheses

The primary variable, transfusion rate, will be measured as the proportion ( $\pi$ ) of patients in each treatment group that is receiving allogeneic blood transfusion of the total number of patients in each treatment group. The hypothesis to be tested is:

$$H_0 = \pi_s = \pi_c$$

versus

$$H_1 = \pi_s \neq \pi_c$$

Where:

$\pi_s$  = Proportion patients treated with Sangvia® that require allogeneic blood transfusion in addition to Sangvia® transfusion.

$\pi_c$  = Proportion patients in the control group that require allogeneic blood transfusion.

The hypothesis will be tested using the Fischer Exact Test. The hypothesis will be rejected if the p-value is  $\leq 0.05$ .

Secondary objectives will be tested using similar hypotheses. The total and variable specific proportion values for infection rate, use of post-operative antibiotics and adverse events will be tested between the groups using the Fischer Exact Test. Continuous variables (e.g. post-op Hb values) will be compared and tested using the Wilcoxon Rank Sum test. Laboratory blood markers will also be evaluated for changes over time within each treatment group and this change will be tested using the Wilcoxon Signed Rank test.

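### The 90% power stated for 260 patients belongs to a large-sample formula; with the Fisher's exact test that the protocol fixes, 260 evaluable patients give 88.8%, and 90% needs 270

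*Protocol*

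**What the plan says.** Section 6.5 of the Protocol bases the sample size on the primary variable, the proportion of patients given allogeneic blood. The planning rates are 21% in the control group ("An estimation normal use of allogeneic blood of 21% is based on reported values in the literature") and about 7% in the test group ("The expected values of transfusion rate in the Sangvia® group is estimated to lie around 7" per cent). On the method it says "The sample size formula used is referred to in Lachin 1981", and it prints the formula with Zα = 1.96 and Zβ = 1.2816. The result "is calculated to 260 patients (5% significance level, two-sided hypothesis, 90% power").

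On attrition it adds "Additional 40 patients will be included in the study to compensate for drop-out", and concludes that "300 patients will be included in total and 150 in each treatment group".

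Section 6.2 names the test for the same hypothesis: "The hypothesis will be tested using the Fischer Exact Test", with rejection at p ≤ 0.05. Section 6.4 and the synopsis repeat this choice for dichotomous variables. Section 6.3 bases efficacy conclusions on the per-protocol set.

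**The concern.** The printed formula rests on the normal approximation and describes the power of a large-sample test of two proportions. Fisher's exact test conditions on the total number of patients transfused. Because the data are discrete, its actual type I error usually lies well below the nominal 5%, and it pays for this in power. Section 6.5 makes no allowance for that. The protocol itself fixes the formula, the number, the power and the test, so this is not a detail left to a statistical analysis plan.

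What is at stake is the accuracy of two design figures: the power at the number called necessary, and the number of patients that can be lost before power falls below 90%. The validity of the test is not in question, since Fisher's test does not inflate the type I error.

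**Working it through.** **Inputs, all from Protocol sections 6.2 and 6.5.** Control rate 0.21, test rate 0.07, mean rate 0.14, two-sided α = 0.05, power 0.90, equal arms, rejection when the two-sided Fisher p-value is at most 0.05.

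**Step 1: the plan's own figure.** N = (Zα + Zβ)² × 4 × π̄ × (1 − π̄) / (πs − πc)²

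- (1.96 + 1.2816)² = 10.508
- 4 × 0.14 × 0.86 = 0.4816
- (0.07 − 0.21)² = 0.0196
- N = 10.508 × 0.4816 / 0.0196 = 258.2

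Rounded up, this supports the stated 260.

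**Step 2: power of the named test.** Let X ~ Bin(n, 0.21) and Y ~ Bin(n, 0.07) be the numbers transfused in the control and test arms. The exact power is the sum of P(X = x) × P(Y = y) over all pairs (x, y) for which the two-sided Fisher p-value is ≤ 0.05. The minimum-likelihood and doubled one-tail definitions of the two-sided p-value gave the same power at every size checked.

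| Evaluable total | Per arm | Exact Fisher power |
|---|---|---|
| 260 | 130 | 88.8% |
| 268 | 134 | 89.9% |
| 270 | 135 | 90.1% |
| 300 | 150 | 93.1% |

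Power stays above 90% at every equal-arm total checked from 270 to 302.

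**Step 3: where the power goes.** The same enumeration with equal rates in both arms, at 130 per arm, gives the actual size of the Fisher test:

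- 2.6% at a common rate of 7%
- 3.3% at 14%
- 3.6% at 21%

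The formula assumes that the full 5% is used.

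**Step 4: what this means for losses.**

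- Power shortfall at 260: 90 − 88.8 = 1.2 points, so the risk of missing the assumed effect is 11.2% rather than 10%.
- Extra evaluable patients for 90%: 270 − 260 = 10, and 10 / 260 = 3.8%.
- Loss implied by section 6.5: 300 − 260 = 40, and 40 / 300 = 13.3%.
- Loss that keeps 90% with Fisher's test: 300 − 270 = 30, and 30 / 300 = 10%.

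**Step 5: sensitivity to the planning rates, at 130 per arm.**

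| Control rate | Test rate | Exact Fisher power |
|---|---|---|
| 21% | 6.75% | 90.2% |
| 21.5% | 7% | 90.6% |
| 21% | 7.5% | 85.6% |

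A quarter-point change in one assumed rate removes the gap, and a half-point change the other way costs more than the gap itself.

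**The case against.** The strongest reply is that 300 patients are enrolled, which gives 93.1% with Fisher's test, and that the protocol does not expect to end with 260. Section 6.1.3 replaces drop-outs before surgery and makes up for those after surgery while recruitment is open; section 3.5 lets replacements come on top of a clinic's planned total. The allowance of 40 is therefore meant only for patients who drop out after surgery and after recruitment has closed. Section 4.2.1.1 assesses the primary outcome up to discharge, so a patient missed at month 2 already has it.

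Most of this stands. A reader might infer that the planned attrition leaves 260 patients in the analysis and that the trial is thus designed to fall short of 90%. The documents do not support that: 260 is the bottom of the drop-out allowance, not the expected number. There is one qualification. The per-protocol set also excludes major deviations (6.3), suspected biased transfusion decisions (3.1, 3.2 and 3.6.1) and incorrect enrolments (3.3.5.3). Section 6.5 ties the 40 to drop-out only, and the protocol gives no expected rate for these exclusions. The final per-protocol number could therefore lie on either side of 270.

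It can also be said that the gap is smaller than the uncertainty in a test-group rate described only as around 7%, and that the interim look in section 6.6 re-examines both rates. The first is true and keeps the point minor. The second does not address it: section 6.6 reacts to rates that differ from those assumed, so if 21% and 7% were confirmed exactly, the mismatch between formula and test would remain.

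**Conclusion.** The point holds as a small inconsistency between the sample size statement and the primary test. For the test fixed in sections 6.2 and 6.4, 260 evaluable patients give 88.8% power rather than 90%, and 90% requires 270. The shortfall of 1.2 points materialises only if more than 30 of the 300 enrolled are lost from the per-protocol set.

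A reader might go further and conclude that 260 is an arithmetic error, or that enrolment must rise. Neither follows. The figure reproduces from the printed formula, and 300 enrolled already covers 270 evaluable patients if losses stay within 10%.

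The figures assume true rates of exactly 21% and 7%, losses that fall equally on the two arms and are unrelated to outcome, independent patients, and an unstratified two-sided Fisher test with rejection at p ≤ 0.05.

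**What to change.** Keep Fisher's exact test and 300 enrolled. Restate section 6.5 to say that, with Fisher's exact test at 21% v 7%, power is 88.8% with 260 evaluable patients, 90% with 270 and 93.1% with 300, so 90% power tolerates 30 losses (10%) from the per-protocol set. It should also be made clear that these losses include per-protocol exclusions as well as drop-out.

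Another way to make the two sections agree would be to keep 260 and name the uncorrected chi-square test. At 130 per arm that test has 91.7% exact power, but its actual size can reach 5.06% (at a common rate of 10%), so it gives up strict control of the type I error. That is a trade-off and is not needed here.

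The cost is a sentence or two in section 6.5 and a slightly less favourable power figure at 260. Enrolment, the primary test and the analysis sets do not change.
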